**Phase 1 and 2 Data and Safety Monitoring, Including Adverse Events**

Phase 1 of the study will utilize a data and safety monitor to enhance participant protection. The individual responsible for data and safety monitoring will be [name], a board-certified, staff psychiatrist at the Durham VAMC with over 25 years of clinical and research experience in brain stimulation techniques. [name] will review adverse events and monitor the safety of participants as well as the quality and completeness of the accrued study data during regularly scheduled meetings. The data monitor will review data quarterly but will also be consulted at any time in the event of study-related, unanticipated and/or serious adverse events. The data monitor performs the critical function of monitoring study adverse events and determining whether a favorable risk-benefit ratio justifies continuation of a given study. The data monitor plays a complimentary role to the Durham VA Institutional Review Board (IRB) and the Duke University IRB, which focus mainly on the prospective review of study protocols (although the IRB may also be involved in halting a study in the face of serious, reportable adverse events. Any concerns raised by the data monitor will be discussed with the PI and mentoring team.

For phase 2 of the study, data monitoring will be completed by a CSR&D-assigned Data Monitoring Committee (DMC). The study team will submit reports to the DMC annually, or as required by the DMC.

The PI will meet at least weekly with study personnel to discuss enrollment, participation, and any adverse events or unanticipated problems. Regular meetings between investigators and the project manager will allow for ongoing progress reports, including the number of participants currently involved in each study, attrition rates, and scheduled data collection from participants, as well as notification and review of any AEs. Safety monitoring for AEs will be conducted in real time by the PI and/or project manager. The following information about adverse events will be collected: 1) the onset and resolution of the AE, 2) an assessment of the severity or intensity (use existing grading scales whenever possible), 3) an assessment of the relationship of the event to the study (definitely, probably, possibly or not related), and 4) action taken (e.g., none, referral to physician, start or increase concomitant medication). The PI will determine the severity of the event, will assign attribution to the event, and will monitor the event until its resolution. Any adverse events will be reported to the DVAHCS and DUMC IRBs in accordance with their Human Research Protection Program’s Standards of Practice. All research projects conducted at DVAHCS and DUMC are required to have yearly IRB review, including a safety review. Additionally, any changes to the project between review periods must be approved by the appropriate IRB prior to fielding.

Based on the study team’s long-term clinical and research experience with patients with high-risk psychiatric disorders such as PTSD, depression, and anxiety disorders, we have developed IRB-approved standards of practice for psychiatric emergencies. These standards have been used for several years. It is not unexpected that participants will experience increased distress associated with the diagnostic clinical interviews. Our extensive clinical and research experience suggest that there is no serious risk in these patients associated with assessment and interview procedures as proposed. Over the past several years, several hundred patients with psychiatric diagnoses have participated in our research team’s clinical trials at DVAHCS and DUMC, and there have been only rare occurrences of serious adverse events (i.e., hospitalization only) due to temporary psychiatric symptom increases.

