**Design**

**Phase 1 Research Design and Methods**: To determine the viability of rTMS as a smoking cessation intervention in a special clinical population of Veterans with comorbid PTSD, we propose to conduct an open-label feasibility study to evaluate the ability to provide and acceptability of rs-fMRI-guided rTMS in Veterans with PTSD who smoke who are receiving standard-of-care for smoking cessation at Durham VA. In addition, we propose to evaluate the ability to recruit and retain Veterans in the feasibility study. A single-arm, open-label feasibility study was chosen based on the specific aims, small sample size limiting statistical analyses, and practical considerations of the CDA-1 including 2-year duration, lack of research funding, and explicitly prohibited RCT design in the CDA-1 funding announcement.

We hypothesize that fMRI-guided rTMS will be safe, feasible, acceptable by Veterans, and we will be able to effectively recruit and retain eligible subjects in the study. We expect to meet the primary endpoints of the proposed project, which will determine successful completion of the study intervention and justification to continue this line of research. Specifically, this will be defined as recruitment of 18 subjects, 14 subjects completing at least 90% of all study procedures (~80% retention rate), and an acceptability rate of  7/10 on a 10-point scale. We also hypothesize that pre-treatment rs-fMRI will provide a cortical target in the right postcentral gyrus that is functionally connected with the insula and accessible by neuronavigated rTMS, therefore establishing the feasibility of the protocol. Exploratory outcomes will include a change in fMRI resting-state functional connectivity between the cortical rTMS target and the insula, therefore demonstrating target engagement. While not the focus of the current study, we will also monitor clinical outcomes to demonstrate if these measures can be collected, including nicotine dependence, cravings, withdrawal, and abstinence (biochemically verified by exhaled carbon monoxide  6 ppm), psychiatric symptoms related to PTSD and depression, and alcohol use.

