Overall Design: Fifty eligible participants will be randomized to one of 2 conditions: active-rTMS + CBT + NRT (n=25) or sham-rTMS + CBT + NRT (n=25). The full randomization sequence will be generated *a priori*. Participants will receive a baseline MRI scan, 5 daily neuronavigated active or sham rTMS treatments the week prior to their quit date, followed by a post-treatment MRI scan. In order to be able to use the fMRI results to inform placement of the TMS coils, there may be up to a two-week lag between the first MRI and the first TMS treatment session. All participants will receive 5 sessions of CBT for smoking cessation in which session 3 is designated as the quit date. All participants will also receive prescriptions of nicotine replacement in the form of 21 mg, 14 mg, and/or 7 mg patches and 2-4 mg nicotine gum or lozenges starting on the quit date and continuing for up to 90 days at individually tapered doses. All rTMS and MRI procedures will occur at Duke University Medical Center (DUMC). Participants will sign a Duke consent form and HIPAA authorization for those procedures.

We hypothesize that neuronavigated rTMS combined with CBT and NRT will be a safe, feasible, and effective method for smoking cessation in our study population. We anticipate being able to effectively recruit and retain eligible subjects in the study. Our primary feasibility endpoint will help determine successful completion of the study intervention and justification to continue this line of research. Recruitment will target enrolling 50 subjects, with a goal of 40 or more subjects completing at least 90% of all study procedures (>80% retention rate). We hypothesize that active- as compared to sham-rTMS will result in greater 7-day point prevalence abstinence rates (biochemically verified by exhaled carbon monoxide < 5 ppm) at end-of-treatment, and 3-month follow-up time points. We also hypothesize that active-rTMS will result in an increase in functional connectivity between the cortical rTMS target and the insula, therefore demonstrating target engagement. We also anticipate network-level differences in rsFC between active- vs sham-rTMS groups. We will also monitor levels of nicotine dependence, cravings, withdrawal, prolonged abstinence, psychiatric symptoms related to PTSD and depression, and alcohol use.

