**Phase 1 and 2 Risk/Benefit Assessment**

**Potential Risks**

Overall, the risks to subjects are low in light of the potential benefits to them for participating in the study, including quitting smoking. Participants may receive satisfaction from contributing to the progress of scientific research.

Study-related serious adverse events are not expected but will be closely monitored and will be reported in accordance with VA, DUMC, and FDA policy.

Study Assessments: Regarding completion of study measures and structured interviews, there is a risk of discomfort or distress in answering questions, especially questions related to traumatic experiences. However, distress and discomfort related to these study activities are usually temporary and well-tolerated. Previous studies in our laboratory that have included trauma- and PTSD-related questionnaires, interviews, and treatment have had no greater than expected adverse events related to study participation. Every effort will be made to make the environment comfortable and supportive during assessment procedures. Risks also include discomfort related to quitting smoking. Quitting smoking will cause nicotine withdrawal that may lead to headaches, nausea, irritability, weight gain, difficulty concentrating, poor sleep, increased appetite, anxious or depressed mood, and craving for cigarettes. There are risks associated with the use of NRT. Minimal risks associated with wearing a nicotine patch include skin irritation, dizziness, lightheadedness, increased heart rate or blood pressure, nausea or vomiting. Inherent to any research, there is also a potential risk associated with the loss of confidentiality of study data.

Please note, risks associated with study procedures that occur at DUMC are described in the Duke IRB protocol and informed consent document.

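### Adverse-event causality is rated only against the study as a whole, so the adverse-event record does not separate rTMS-related events from those of NRT, quitting, MRI or assessments, chiefly in single-arm Phase 1 and for individual serious events

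*Protocol*

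**What the plan says.** The Protocol section *Phase 1 and 2 Data and Safety Monitoring, Including Adverse Events* lists four items to collect for each event: timing ("1) the onset and resolution of the AE"), severity, causality and action taken. Causality is "an assessment of the relationship of the event to the study (definitely, probably, possibly or not related". The section adds that "The PI will determine the severity of the event, will assign attribution to the event", but names no target for that attribution other than the study.

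The Protocol also describes effects expected from components other than stimulation:

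- Quitting (*Potential Risks*): "Quitting smoking will cause nicotine withdrawal that may lead to headaches, nausea, irritability, weight gain, difficulty concentrating, poor sleep".
- NRT (same section): "Minimal risks associated with wearing a nicotine patch include skin irritation, dizziness, lightheadedness, increased heart rate or blood pressure, nausea or vomiting".
- Interviews (safety monitoring section): "It is not unexpected that participants will experience increased distress associated with the diagnostic clinical interviews".

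It does not list the risks of rTMS and MRI. *Potential Risks* refers the reader to the Duke IRB protocol and consent form, which are not at hand.

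Safety is hypothesised in both phases. The Phase 1 design text says "We hypothesize that fMRI-guided rTMS will be safe, feasible, acceptable by Veterans". The Phase 2 design text applies the claim to the package: "neuronavigated rTMS combined with CBT and NRT will be a safe, feasible, and effective method".

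**The concern.** A relationship-to-study rating informs about a device only if the device is the main thing in the study that can cause events. Here it is one of several. A withdrawal symptom, a patch reaction and a stimulation effect can each be rated definitely related, and each rating would be correct.

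Two uses of the record suffer. In Phase 1 there is no control arm, so event-level attribution is the natural way to decide which adverse events count against rTMS. For a single serious event in either phase, the IRBs and monitors need a view on the device, and a group comparison cannot supply one. The Phase 1 monitor is also to be consulted between quarterly reviews about events that are study-related, unanticipated or serious. A label that covers ordinary withdrawal makes the first of those triggers less specific.

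A judgement not recorded when the event occurs cannot be rebuilt reliably at analysis, so this cannot be left to an analysis plan.

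**Working it through.** The Protocol gives no adverse-event rate or safety sample size, so there is no figure to reproduce. The check is a comparison of its sections, with some arithmetic for context.

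**Step 1: what the study contains and when.**

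| Component | Timing in the Protocol | Effects the Protocol names |
| --- | --- | --- |
| Diagnostic interviews | Baseline | Distress |
| rTMS or sham | Five days in the week before the quit date, with cue provocation beforehand | Referred to the Duke documents |
| MRI | Before the course, and 1 to 24 hours after the last session | Referred to the Duke documents |
| Quit attempt | From the quit date | Headache, nausea, poor sleep, mood change and others |
| NRT | Phase 2 *Overall Design*: starts on the quit date. *Phase 1 and Phase 2 Study Interventions*: prescribed at medical screening | Skin irritation, dizziness, nausea and others |

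**Step 2: apply the rating.** Take a report of nausea. The Protocol lists it under both withdrawal and the patch. A rater certain that the patch caused it codes it definitely related to the study. A rater certain that stimulation caused it enters the same code. The rating does not change with the component.

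**Step 3: can the other recorded items recover the cause?** Only in part.

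- *Onset dates* help to separate baseline interviews, and withdrawal after the quit date, from the rTMS week. They do not cleanly separate cue provocation (before the stimulation) or the second scan (1 to 24 hours after the last session). For NRT, the two statements on when it begins differ and must be reconciled.
- *The TMS Side Effects Scale* is given in Phase 1 at the post-rTMS/quit-date and 2-week assessments (Table 1), and in Phase 2 at the quit date, end of treatment and 3 months (Table 2). *SUDS* covers distress during TMS, and the *MNWS-R* covers withdrawal. These measure symptoms separately and are useful, but none assigns a cause to a reported adverse event.

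**Step 4: does the design answer the question without the rating?**

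- *Phase 1: no.* There is one arm. If no rTMS-related event occurred, the one-sided 95% upper bound on its rate would be 1 − 0.05^(1/n): 15.3% for n = 18 enrolled and 19.3% for n = 14 completers. Using that bound requires knowing which events count as rTMS-related, which the study-level rating leaves undefined.
- *Phase 2: yes, for active against sham stimulation.* Both arms receive the same CBT and NRT, so the difference in all adverse events by type estimates the effect of active stimulation. Effects common to both arms, such as coil contact, cue provocation and MRI, cancel and are not identified.

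**Step 5: what limits Phase 2.** With 25 per arm and two-sided alpha of 0.05 (assumed), power is about 33% for 20% v 40%, 61% for 20% v 50% and 85% for 20% v 60%. Even with perfect attribution, assumed rates of 30% v 10% give a 20-point difference with 95% half-width 1.96 × √(0.30×0.70/25 + 0.10×0.90/25) = 1.96 × √0.012 = 0.215, an interval that still includes zero. All these rates are assumptions. In Phase 2, sample size is the main limit on the group comparison, not the causality wording.

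**The case against.** The strongest case against the point has five parts.

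- **Phase 2 is randomised against sham.** This stands. A reader might infer that the trial cannot tell whether rTMS is safe. The documents do not support that, because the between-arm comparison of all events is valid without any causality rating, within the limits of 25 per arm.
- **rTMS effects and withdrawal have their own instruments.** This stands in part. It would be wrong to say that stimulation effects and withdrawal are captured identically throughout the trial. The gap is confined to the adverse-event record and its causality item.
- **No section judges safety by a count of study-related events.** This stands. A reader might go on to calculate how background events dilute such a count between arms. Any such figure would rest on invented rates and on an endpoint the Protocol never names. Moreover, the Phase 2 hypothesis concerns the combination, for which a study-level rating is not unreasonable.
- **Device attribution may be defined in the Duke protocol, the adverse-event form or a standard procedure.** This cannot be excluded. But the Protocol refers to the Duke documents for risks, not for attribution, and its own section covers both phases and reports to both IRBs.
- **Phase 1 is small enough for case-by-case review.** There are 18 people, weekly meetings and a monitor experienced in brain stimulation. This lowers the stakes. But a case-by-case judgement that is not written down is exactly what the extra field would preserve.

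**Conclusion.** The point holds in a limited form. The Protocol fixes one causality rating, against a study with several components whose expected effects are all properly study-related. The adverse-event record therefore does not distinguish rTMS-related events from those due to NRT, quitting, MRI or assessments. The consequence is real for Phase 1, where rTMS itself is hypothesised to be safe without a comparator, and for individual serious events in either phase. It is slight for the Phase 2 group comparison.

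No numerical size can be given, because the Protocol states no event rates. The weight is modest, and the case for change rests on its low cost and on the difficulty of recovering attribution later. The conclusion assumes that no document outside the Protocol already requires component-level attribution.

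**What to change.** In *Phase 1 and 2 Data and Safety Monitoring, Including Adverse Events*:

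1. Keep the rating against the study as a whole for IRB reporting.
2. Add a rating on the same four levels for rTMS or sham stimulation, and separate ratings for MRI, NRT, quitting/withdrawal and assessments, made when the event is recorded.
3. State that in Phase 2 these ratings are made by a rater blinded to arm. The Protocol gives attribution to the PI and says that participants and two further people are blinded, but with names removed it cannot be seen whether the PI is one of them.
4. In Phase 2, report all adverse events by arm first, with stimulation-attributed events alongside.
5. Reconcile the two statements on when NRT begins, since they affect how onset dates are read.

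The text says that Phase 1 data informed the Phase 2 parameters, so some Phase 1 events may already be recorded. Component ratings added to those should be labelled retrospective.

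The cost is a few fields on the adverse-event form and a short addition to the text, with no extra visits. The drawback is that attribution is a judgement, and some events will be rated possibly related to several components. That is why the comparison of all events by arm should come first.

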**Phase 1 and 2 Risk/Benefit Assessment**

**Potential Risks**

Overall, the risks to subjects are low in light of the potential benefits to them for participating in the study, including quitting smoking. Participants may receive satisfaction from contributing to the progress of scientific research.

Study-related serious adverse events are not expected but will be closely monitored and will be reported in accordance with VA, DUMC, and FDA policy.

Study Assessments: Regarding completion of study measures and structured interviews, there is a risk of discomfort or distress in answering questions, especially questions related to traumatic experiences. However, distress and discomfort related to these study activities are usually temporary and well-tolerated. Previous studies in our laboratory that have included trauma- and PTSD-related questionnaires, interviews, and treatment have had no greater than expected adverse events related to study participation. Every effort will be made to make the environment comfortable and supportive during assessment procedures. Risks also include discomfort related to quitting smoking. Quitting smoking will cause nicotine withdrawal that may lead to headaches, nausea, irritability, weight gain, difficulty concentrating, poor sleep, increased appetite, anxious or depressed mood, and craving for cigarettes. There are risks associated with the use of NRT. Minimal risks associated with wearing a nicotine patch include skin irritation, dizziness, lightheadedness, increased heart rate or blood pressure, nausea or vomiting. Inherent to any research, there is also a potential risk associated with the loss of confidentiality of study data.

Please note, risks associated with study procedures that occur at DUMC are described in the Duke IRB protocol and informed consent document.

**Phase 1 and 2 Protection Against Risk**

Participants are informed clearly during the initial informed consent process that the study is voluntary, and that they may refuse to answer any items that they do not wish to answer on the questionnaires and interviews. They are also informed that they are free to decline participation in any procedure and can withdraw from the study at any time.

Our study team has an established IRB-approved standard of practice (SOP) for the evaluation of risk of suicide and homicide. All study staff members are trained in use of the psychiatric emergencies SOP by a Ph.D. or Masters Degree-level clinician with years of experience in working with persons with psychiatric disorders. The SOP includes a thorough risk assessment including evaluation of risk factors and protective factors associated with both suicide and homicide. Also included in the policy are differential recommendations for action based on determinations of low, moderate, or high risk. Any staff member conducting an interview in which moderate or high risk is determined will contact a senior staff person with clinical expertise in risk assessment, including the PI, co-investigator(s), and/or DVAHCS’s Psychiatric Emergency Clinic or the Emergency Department.

At several time points throughout the study, participants are reminded that they are asked to inform the study therapist, study coordinator, or study PI if they experience a psychiatric emergency such as homicidal or suicidal ideation. Finally, participants are provided the telephone number of study staff who they can call in the case of psychiatric emergencies, including an after-hours contact number.

To ensure confidentiality, all records will be identified by the participant’s identification number, not by name. All raw hard copy data will be kept in a locked file cabinet in a locked room on DVAHCS property. Data files will be stored in a limited access folder on a secure server to which only study staff members have access.

Only the study PI, co-investigators, study physician, project coordinator, and research assistants will have access to private health information (PHI) as part of the study. All staff with access to PHI will be required to complete Privacy Awareness and HIPAA Awareness educational modules. Data are managed and protected in accordance with the research data and safety standards of practice at DVAHCS and DUMC. All project staff will complete educational units required by the DVAHCS and DUMC IRBs, which include information security, privacy awareness, and human subjects’ protection.

